### 2.2. Hospital Group

#### 2.2.1. Cardio-pulmonary Rehabilitation Group Program Conducted in Face-to-Face Format at the Hospital

Due to the current absence of standardized exercise physiology protocols in pediatric cardiology [22], we developed a structured program based on cardio-pulmonary physiology and the limited scientific evidence available up to the present moment [13,23,24]. The sessions were group-based (2–3 patients) and supervised by a pediatric physiotherapist, a pediatric nurse, and a pediatrician specialist in cardiology or a pediatric rehabilitation doctor. Patients were encouraged to maintain their habitual activities during the protocol.

The program will take place twice a week for 12 weeks.

Components of the program:Respiratory Physiotherapy Program: This part of the program incorporates two distinct device-based respiratory training modalities. Our literature review found no previous documentation of respiratory physiotherapy protocols specific to different CHD classifications [13,23,24,25,26] except for patients with Fontan circulation where only techniques with inspiratory muscle training (IMT) devices [27,28,29] or educational sessions with respiratory awareness techniques [30] were used. The objective is to increase inspiratory volume, since most of the patients with CHDs have a restrictive ventilatory pattern (to be determined after ergo-spirometry analysis) and weakness of the respiratory muscles [31]. Children with obstructive or mixed respiratory patterns will also benefit from this program. Improvements in lung inflation have a direct impact on bronchial obstruction.

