#### 2.2.2. Study Group—Home-Based Cardio-pulmonary Rehabilitation Group

Patients assigned to this group will perform the CRP at their own home. The prescribed physical exercise will be uploaded in video format on the TELEA platform belonging to Galician Health Service (SERGAS). The patients will attend the hospital once at the beginning of the study to learn the program with the physiotherapist, who will tell them what their training heart rate is and the safety ranges in which they should move, and once again at the end of the first month. The program will take place twice a week in their home for 12 weeks. Patients will be encouraged to maintain their habitual activities during the protocol.

Components of the program:Respiratory Physiotherapy Program: Children will use two types of respiratory training with devices—COACH and IMT. The home-based rehabilitation program will follow the same respiratory physiotherapy regimen as the hospital-based group, except for the final phase of incremental resistance in IMT. These children will attend the hospital in person only at the start of and at the end of the first month. They will perform three sets of ten repetitions at 30% of the maximum tested in the first month. Once the first month is over, the maximum will be calculated again, and work will be performed at 60% of this value.

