#### Outcomes (Table 2)

Assessment of respiratory function/spirometry: Spirometry is the study of choice in pulmonary function laboratories. The parameters it measures are the volume of air that the child breathes in or out in absolute value or related to time; and it is shown in the volume/time curve [33]. It also measures the flow expressed in curves with the flow/volume ratio. The mediations can be simple if slow breathing maneuvers not dependent on time are used or forced if maximum effort is requested in the shortest possible time, thus allowing the study of dynamic volumes and forced flows. The recording will be on a flow/volume curve. The most useful functional parameters obtained after spirometry are forced vital capacity (FVC), forced expiratory volume in the first second (FEV1), maximum expiratory flow (PEF), and the Tiffeneau index FEV1/FVC, FEF25%, FEF50%, FEF75%, FEF25–75%. [34]. The recording is called a spirogram.Classify, based on the results of spirometry, whether the child has restrictive [35], obstructive, or mixed ventilatory pattern:Restrictive pattern: defined as FVC and FEV1 < 80% of the predicted value, with FEV1/FVC > 80% or normal.Obstructive pattern: defined as FEV1/FVC ratio < 70%, FEV < 80%, and normal FVC.Mixed pattern: defined as FEV1 < 80%, FVC < 80%, and FEV1/FVC ratio that may be normal, increased, or decreased.Exercise capacity: Pediatric treadmill ergo-spirometry will be used. This test allows a non-invasive evaluation of the child’s functional capacity by calculating maximum oxygen consumption. It will be performed in our hospital on a treadmill following the Bruce protocol [36]. The Bruce protocol is a diagnostic tool increasingly used in the outpatient follow-up of these patients, in order to obtain an objective evaluation of the exercise capacity of children with CHDs and to know their real physical situation. It also has undeniable value for prescribing an individualized rehabilitation and physical exercise program. Exercise intensity is determined based on heart rate. This will be determined within the transition zone between the first ventilatory threshold (VT1) and the second ventilatory threshold (VT2). The values obtained in ergo-spirometry performed 6 months prior to the start of the intervention program will be used. Within two weeks after completing the cardio-respiratory physiotherapy program, a new test will be performed for comparative analysis.Quality of life: quality of life questionnaires for children and adolescents with heart disease—PedsQL^™^ 4.0 Generic Core Scales and PedsQL™ Cardiac Module 3.0.

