
**Table 2 jcm-14-00816-t002:** Evaluation protocol.

Measurements	Variable	Material and Methods	Unit of Measurements	Measurements	
				Pre	Post
Lack of adherence to the protocol	Absence	Absence in more than 20% of the sessions	Absence equivalent to missing 5 out of the 24 planned sessions		
Anthropometric data	Circumference of body	Flexible tape measure	cm	X	X
	Composition	Bioelectrical impedance	% body fat	X	X
	Height	Height meter	m/cm	X	X
	Weight	Bascule	kg	X	X
Ergo-spirometry	Oxygen consumption	Ergometer and Treadmill	VO_2_	X	X
Respiratory function	FEV1, FVC, FEV1/CVF, PEF, FEF25%, FEF50%, FEF75%, FEF25–75%	Spirometry	%	X	X
	Respiratory Pattern		Restrictive, Obstructive, and mixed	X	X
Perceived effort	Effort	Modified Borg scale	0–10	X	X

Note: m = meter; cm = centimeter; kg = kilogram; FEV1 = Forced expiratory volume in 1 s; FVC = Forced vital capacity; FEV1/CVF = Tiffeneau index; PEF = maximum expiratory flow; FEF = forced expiratory flow.

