### 2.4. Sample Size

Since no information has been found on the magnitude of the effect on the topic studied, an effect size of 0.8 has been set, taking into account the scale proposed by Cohen and meta-analysis on the effect of rehabilitation in other respiratory conditions [37]. Sample size calculation was performed for a mean difference analysis of independent groups. The effect size was d = 0.8 alpha level of 0.05, power 80%. The estimated sample size was 26 subjects per group. Considering losses of 10%, the number of subjects needed was 56 subjects. G*Power 3.1 software was used to calculate the sample size.

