The success of CRPs relies on the collaboration of multidisciplinary healthcare teams with specialized expertise and addressing the high associated costs. Adherence challenges are particularly prevalent in hospital-based CRPs, which is why home-based programs are increasingly favored. These home interventions not only reduce costs but also diminish the burden on families. The challenge remains to demonstrate that the benefits in quality of life and functional outcomes are at least equivalent to those achieved in clinical settings [13,14,15].

Incorporating respiratory physiotherapy into CRPs is logical, given that CHD patients often experience impaired pulmonary function, contributing significantly to morbidity and mortality. These impairments are frequently due to restrictive respiratory patterns resulting from thoracotomies, sternotomies, and ventilatory muscle weakness, which collectively worsen lung function [41]. Exploring the potential of specific respiratory physiotherapy techniques, such as volumetric incentive spirometry and IMT, in conjunction with physical exercise, could strengthen respiratory muscles and address cardio-respiratory dysfunction in this population. Although preliminary studies have begun to evaluate the effects of IMT on lung and exercise capacity in pediatric CHD patients [28,42], research remains limited. We propose expanding CRPs to include targeted interventions for enhancing inspiratory volume, and strengthening ventilatory muscles may have broader implications for improving the health status of pediatric CHD patients. Given the scarcity of research in this area, further investigations are required to establish a foundation for optimizing rehabilitation strategies.

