### 3.1. Limitations

The results are subject above all to the type of family from which the patients come, influencing the economic level. At this point, and so that this bias is minimized, we propose in our program to provide families with financial transportation assistance in case of belonging to the in-person group.

Children with CHDs are accompanied by high comorbidity. Changes in the process could mean the loss of some subjects from the study. However, we consider that this limitation is the norm in any complex clinical process such as the one at hand.

Children and adolescents suffering from CHDs have been subjected to numerous surgical interventions, medical consultations, and check-ups that have caused multiple absences in their school life. This could cause a lack of adherence to treatment or possible dropouts, especially during the examination stages.

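### The post exercise test is triggered by finishing the programme, so a child who stops early has no scheduled peak VO2 value and the hospital-versus-home comparison risks being limited to finishers

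*Protocol article*

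**What the plan says.** The Outcomes part of section 2.3 sets the timing of the repeat ergo-spirometry: "Within two weeks after completing the cardio-respiratory physiotherapy program, a new test will be performed for comparative analysis". This is the only timing rule for any post assessment in the article.

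- **Table 1** lists a first and a second visit, both before the programme. It has no post visit.
- **Table 2** marks spirometry, oxygen consumption and other measures as Pre and Post, without dates. It defines lack of adherence as "Absence in more than 20% of the sessions", equated to 5 of 24, and attaches no consequence for testing or analysis.
- **Programme length** is the same in both arms. Section 2.2.1 (hospital): "The program will take place twice a week for 12 weeks". Section 2.2.2 (home): "The program will take place twice a week in their home for 12 weeks".
- **Expected losses.** Section 2.4: "Considering losses of 10%, the number of subjects needed was 56 subjects". Section 3.1, on the burden of earlier care and missed school: "This could cause a lack of adherence to treatment or possible dropouts, especially during the examination stages". Section 3, on programmes of this kind in general: "Adherence challenges are particularly prevalent in hospital-based CRPs".
- **Analysis.** Section 2.6 compares group means by a t test, Welch test or Mann–Whitney test and names no analysis set.

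**The concern.** The main objectives are to improve respiratory function and exercise capacity and to compare the hospital and home programmes. Peak VO2 carries the exercise-capacity part. Its post value is tied to an event that follows randomisation and that the assigned arm can influence.

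A child who stops at, say, week 6 has not completed the programme, so the rule never calls for a test. If staff follow the text, that child has no post peak VO2. Should the children who stop be less fit or less motivated than those who finish, the arm with more stopping is judged on its better children, and the balance that randomisation provided is weakened.

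This is a matter of data collection and not of detail left to an analysis plan. An analysis plan can say that all children are analysed in their assigned arm, but it cannot recover a measurement that was never taken.

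**Working it through.** **1. The plan's own figure.** Inputs from section 2.4: "The effect size was d = 0.8 alpha level of 0.05, power 80" (per cent). A two-sample t test, two-sided, with 1:1 allocation and the noncentral t distribution gives 25.52, so 26 per group, with power 0.807. The stated 26 is reproduced. For 10% losses, 52 / 0.90 = 57.8, so 58. The stated 56 is two fewer, which is small and does not affect this point.

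**2. Is a test scheduled for a child who stops early?** The places that could schedule one:

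| Place | Content | Covers an early stopper? |
|---|---|---|
| Section 2.3, Outcomes | test counted from completion | No |
| Table 1 | pre-programme visits only | No |
| Table 2 | Post crosses, no date, no attendance condition | Not stated |
| Section 2.6 | test methods only | No |

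No place counts the test from randomisation or from programme start.

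**3. Bias if only finishers are measured.** In one arm, let p be the proportion who do not finish and g the mean of finishers minus the mean of non-finishers, in SD. The mean of all children is (finisher mean) − p × g, so the finisher mean is too high by p × g. The arm difference is therefore biased by

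p(hospital) × g(hospital) − p(home) × g(home),

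which with a common g is g × [p(hospital) − p(home)].

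The article gives neither p by arm nor g, so every input below is an assumption:

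| Non-completion, hospital vs home | g = 0.5 SD | g = 1.0 SD |
|---|---|---|
| 10% vs 10% | 0 | 0 |
| 20% vs 10% | 0.10 × 0.5 = 0.05 | 0.10 × 1.0 = 0.10 |
| 30% vs 10% | 0.20 × 0.5 = 0.10 | 0.20 × 1.0 = 0.20 |

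Against d = 0.8 the non-zero range is 0.05 / 0.8 = 6% to 0.20 / 0.8 = 25%. With g positive, the bias favours the arm with more loss.

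**4. Power if the values are missing** (equal loss in both arms, d = 0.8, two-sided 5%):

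| Randomised | 10% loss | 20% loss | 30% loss |
|---|---|---|---|
| 56 (section 2.4) | 0.795 | 0.744 | 0.684 |
| 52 (26 per arm, abstract) | 0.763 | 0.711 | 0.650 |

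The 10% column is what the plan already accepts. Testing children who stop recovers some of this loss.

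**The case against.** The strongest reply is that the programme has a fixed length of 12 weeks in both arms. Completing it can then simply mean that the 12 weeks have passed, which puts the test at about weeks 12 to 14 for everyone. The article never defines completion as attending all 24 sessions. This reading is reasonable and would remove most of the problem, but the text does not state it, and a child who has left the programme is not obviously included in it.

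Several stronger readings are tempting and are not supported:

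- **That the trial will analyse finishers only.** No such set is stated. Analysis sets and missing data may be covered in a full protocol or analysis plan that is not shown.
- **That a child who falls behind gets no test.** Such a child is still tested, either at the end of the 12 weeks or somewhat later.
- **That made-up sessions delay the test by some weeks.** The article mentions no make-up sessions, and Table 2 counts absences as missed.
- **That spirometry is left without a window by design.** Table 2 gives it no date, but it may well share the ergo-spirometry session.
- **That loss will be greater in the hospital arm.** The remark in section 3 concerns such programmes in general. The 10% allowance is not split by arm, and travel help (section 2.5 for both groups, section 3.1 for the in-person group) may reduce hospital losses.

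It is also true that a reworded window does not prevent children from refusing the examination itself, which is where section 3.1 particularly expects dropouts. What stands after all this is the child who stops early: the written rule schedules no test, although losses are expected.

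**Conclusion.** The point holds in a limited form. The trigger for the post exercise test is fixed badly: as worded it leaves early stoppers without a scheduled peak VO2, so the randomised comparison on that outcome risks resting on those who finish.

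The size of any bias cannot be determined from the article. The range of 0.05 to 0.20 SD depends wholly on the assumed rates and gap, and the bias vanishes when loss and gap are the same in both arms. It illustrates what could happen and is not an estimate for this trial.

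This is an inexpensive improvement and not a fault that invalidates the design. It should be made before children reach the end of the programme, because the missing measurements cannot be obtained afterwards.

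**What to change.** Replace the timing sentence in the Outcomes part of section 2.3, and add a matching Post visit to Table 1, along these lines:

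*Ergo-spirometry and spirometry will be repeated between weeks 12 and 14 after the scheduled programme start in every randomised child, whatever the number of sessions attended and including children who stop the programme, unless consent to follow-up is withdrawn or the responsible physician judges that the test is not possible. These children are analysed in the arm to which they were assigned.*

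The window uses the protocol's own 12 weeks and its own two-week allowance. Counting from the scheduled start also covers a child who never begins. The exception for clinical reasons is needed because section 3.1 expects comorbidity to cause some losses. Recording the reason for each missing test would show whether loss differs by arm.

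**Cost.** One sentence, one table row, and a few extra tests of a kind already planned: at the plan's 10% loss, at most about six (0.10 × 56 = 5.6). The estimated effect may be slightly diluted compared with finishers only. Sample size, programme content and test method are unchanged.

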### 2.4. Sample Size

Since no information has been found on the magnitude of the effect on the topic studied, an effect size of 0.8 has been set, taking into account the scale proposed by Cohen and meta-analysis on the effect of rehabilitation in other respiratory conditions [37]. Sample size calculation was performed for a mean difference analysis of independent groups. The effect size was d = 0.8 alpha level of 0.05, power 80%. The estimated sample size was 26 subjects per group. Considering losses of 10%, the number of subjects needed was 56 subjects. G*Power 3.1 software was used to calculate the sample size.

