## Abstract

**Background/Objectives:** Children who suffer from congenital heart defects (CHDs) have a decreased ability to perform physical exercise and consequently have a decrease in their functional capacity. The main causes of this decrease in functional capacity have been related on the one hand to residual hemodynamic defects and, at the same time, to a situation of physical deconditioning due to inactivity, as well as problems in lung function, especially the presence of restrictive patterns that influence the amount of O_2_ insufflated (decreased maximum VO_2_), consequently generating a deficient maximum O_2_ consumption and maximum work rate. This represents an important prognostic value, since it constitutes an independent predictor of death and hospitalization. This study aims to determine the benefits obtained regarding respiratory function, exercise capacity, and quality of life after implementing a hospital-based cardio-respiratory rehabilitation program compared to a home-based Cardio-respiratory Physical Activity Program in patients with intervened CHDs. **Methods**: This is a randomized controlled trial on the effectiveness of two different rehabilitation programs on respiratory function, exercise capacity, and quality of life in patients with CHDs conducted at the Child Cardiology and Congenital Heart Disease Unit of the University Hospital Complex of A Coruña (CHUAC). There will be two groups: Cardio-respiratory rehabilitation group program conducted in a face-to-face format at the hospital (*n* = 26) and a study group that follows a home-based Cardio-respiratory Physical Activity Program (TELEA) (*n* = 26). The measurement variables will be respiratory function, forced vital capacity (FVC), forced expiratory volume in the first second (FEV1), maximum expiratory flow (PEF), the Tiffeneau index (FEV1 /FVC), forced expiratory flow (FEF25%, FEF50%, FEF75%, FEF25–75%), exercise capacity (peak VO_2_), and the quality of life of these children and their families. **Conclusions**: The implementation of cardiac and pulmonary rehabilitation programs in children with CHDs is essential to improve their quality of life, exercise tolerance, and socialization. These programs optimize life expectancy and promote integration, being crucial for their physical and emotional well-being

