### 2.6. Data Analysis

The normality of the data distribution was analyzed with the test of Kolmogorov–Smirnov. For the descriptive analysis, the mean and standard deviation were used if the distribution of the variables was normal; otherwise, the median and interquartile range were calculated. The qualitative variables of the study will be defined by frequencies and percentages.

Student’s *t* test will be used to compare the intergroup means if the distribution of the variables is normal. The non-parametric Mann–Whitney U test will be applied if the normality of the data is not fulfilled. Levene’s test will be used to test the equality of variances between groups. Welch’s *t*-test will be used if the assumption is not met. Repeated measures t-test or the non-parametric Wilcoxon t-test will be applied for the comparison of intragroup means depending on the normality of the data. The Chi-Square test will be used to test the association between categorical variables.

A confidence level of 95% will be considered for the calculation of the confidence intervals and a significance level of 5% for the statistical tests. The statistical program IBM SPSS Statistics version 28.0.1 will be used to analyze the data.

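### The Abstract plans two groups of 26 (52 children) while Section 2.4 requires 56 after losses; power is about 76.5% if 52 governs and about 79–80% if 56 governs

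*Protocol article*

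**What the plan says.** Section 2.4 (Sample Size) of the protocol article sets the basis of the calculation: "Sample size calculation was performed for a mean difference analysis of independent groups". The inputs follow: "The effect size was d = 0.8 alpha level of 0.05, power 80"%. The result is "The estimated sample size was 26 subjects per group", and the section then allows for dropout: "Considering losses of 10%, the number of subjects needed was 56 subjects". Section 2.5 (Randomization) specifies 1:1 allocation, so 56 means 28 per arm.

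The Abstract gives other group sizes. The hospital arm is described as "Cardio-respiratory rehabilitation group program conducted in a face-to-face format at the hospital (*n* = 26") and the home arm as "a study group that follows a home-based Cardio-respiratory Physical Activity Program (TELEA) (*n* = 26"). Together that is 52. The Abstract does not say whether these are children randomised or children with outcome data, and no other section of the article settles it.

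**The concern.** The Abstract's 26 per arm equals the number that Section 2.4 needs before any loss. Read as the planned group size, it removes the loss allowance that Section 2.4 adds, and a reader cannot tell whether 52 or 56 children are to be randomised.

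This matters because 26 per arm has almost no slack: losing a single child from one arm takes power just below 80%. The plan assumes a 10% loss, and Section 3.1 (Limitations) expects losses from comorbidity and dropouts around the examinations, which is where outcome data are collected. The loss allowance is therefore what protects the stated power. A later report will also be compared with one planned number, and the article prints two.

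**Working it through.** **Inputs.** From Section 2.4: d = 0.8, alpha 0.05, power 80%, two independent groups, 26 per group, 10% loss, total 56. From the Abstract: 26 + 26 = 52. From Section 2.5: 1:1 allocation. Sidedness is not stated; Section 2.6 (Data Analysis) gives only "a significance level of 5% for the statistical tests". Two-sided is assumed because it reproduces the plan's figure, as step 1 shows.

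**Formula.** For n1 and n2 evaluable children, the two-sample t-test has df = n1 + n2 − 2 and noncentrality d × √(n1·n2/(n1 + n2)). Power is the probability that the noncentral t exceeds the two-sided 5% critical value in absolute size.

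**Step 1: reproduce the plan's figure.** Solving for 80% power at d = 0.8 gives n = 25.52, rounded up to 26 per group, which matches. At 26 + 26 the noncentrality is 0.8 × √(676/52) = 0.8 × √13 = 2.88 on 50 df, and power is 80.7%. A one-sided test would need only 20.03, so 21 per group, which does not match.

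**Step 2: expected evaluable numbers after 10% loss.**
- 52 randomised: 52 × 0.9 = 46.8, about 47.
- 56 randomised: 56 × 0.9 = 50.4, about 50.
- 58 randomised: 58 × 0.9 = 52.2, about 52.

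**Step 3: power at those numbers.**

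| Randomised | Evaluable (arms) | Power |
|---|---|---|
| 52 | 23 + 23 | 75.6% |
| 52 | 23 + 24 | 76.5% |
| 52 | 24 + 24 | 77.4% |
| 56 | 25 + 25 | 79.1% |
| 56 | 25 + 26 | 79.9% |
| 58 | 26 + 26 | 80.7% |

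For 52, the 23 + 24 row is nearest to 46.8; the rows on either side show the effect of rounding. At 23 per arm, the effect detectable with 80% power is d = 0.845 instead of 0.80.

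**Step 4: the loss allowance itself.** Keeping 52 evaluable after a 10% loss needs 52/0.9 = 57.8, so 58 (29 per arm). Adding 10% instead gives 52 × 1.1 = 57.2, which also rounds up to 58. A total of 56 leaves 52 evaluable only if no more than 4/56 = 7.1% are lost. The gap is two children, and by step 3 it takes power from 80.7% to between 79.1% and 79.9%, a difference of 0.8 to 1.6 points.

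**The case against.** The best defence is that Section 2.4 is the operative section. It includes a loss allowance and asks for 56. The Abstract never says that 26 is the number enrolled, and since 26 is exactly the pre-loss figure of Section 2.4, it may just repeat the analysable number. On that reading power after losses is within about a point of 80%; with no losses at all, 28 per arm would give 83.6%. Even in the worse case the shortfall is about 3 to 4 points. The effect size of 0.8 is a conventional choice, made because no information on the effect was found, so a shift to 0.845 lies well within its uncertainty.

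Much of this stands. A reader might infer that the trial cannot deliver its stated 80% power, or that both printed totals fail it. The article does not support that. The material shortfall arises only if 52 is the number randomised, which is not established, and the shortfall at 56 is too small to matter in practice.

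The defence does not remove the conflict. The Abstract attaches 26 to each group that is to be formed, without a qualifier. If evaluable children are meant, the article needs to say so; if Section 2.4 governs, the Abstract is wrong. Nor is this detail lost in condensing a longer protocol: both figures are printed, and they disagree.

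**Conclusion.** The two planned sizes conflict, and the Abstract's is the number before losses. If 52 are randomised, the stated 80% becomes about 76.5%. If 56 are randomised, the stated power is essentially met and only the Abstract needs correcting. The 56-versus-58 difference is secondary. This is a consistency error of minor to moderate weight; the core calculation of 26 per group is correct.

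The figures assume a two-sided t-test, a true effect of d = 0.8, a 10% loss spread about evenly over the arms, and losses that reduce numbers without biasing the comparison.

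**What to change.** Give one randomised total in both the Abstract and Section 2.4, and label 26 per group as the evaluable number. Then state the power that goes with that total after 10% loss: about 76–77% for 52, about 79–80% for 56, or about 81% for 58. Choose 58 (29 per arm) if 26 evaluable per arm is to be kept at the stated loss. State in Section 2.4 that the calculation is two-sided, if that is so.

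Keeping 56 costs only wording: the Abstract changes to 28 per arm. Keeping 52 means printing a lower power. Moving to 58 means recruiting two more children than Section 2.4 now requires.
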